### Sample size and power calculation

The sample size was calculated using an online sample size calculator (CinCalc.com) to detect a 20% difference in mean EPDS scores between the intervention versus control groups with a 80% power and an alpha of 0.05 in each study location.^50^ EPDS scores show a normal distribution with a mean of 12.5 and SD of 4.0.^51^ A difference of 20% in the primary outcome is of clinical relevance with regards to the symptomatology of PPD.^52^ Based on this, the calculated sample size is 40 participants in each arm (intervention/control) of the study in each study location (n=80 participants per city). Taking into account and possible dropouts, we estimated a required sample size of 100 participants for each city (study location). The same principle will be applied if any additional study locations are added to this multicentre RCT.

### Data management

Each study participant will receive a study number for identification. Data will be collected continuously and through the smartphone application entered into an electronic case report system. Data will be encrypted and safely stored on an electronic server at the Karolinska Institute in Stockholm, Sweden in compliance with European general data protection regulation. Anonymised data will be extracted from the electronic case report system after data collection has ended and analysed for the different endpoints.

### Statistical methods

Data will be analysed per protocol using an intention-to treat method. Average EPDS, GAD7 and IES-R scores will be compared between the intervention and control groups and across time points (prenatal and postnatal), using independent sample t-tests. Differences in proportions will be assessed using χ^2^ test. The non-normally distributed continuous variables will be analysed with the Mann-Whitney U test, and the results of the intervention will be analysed by Cohen’s effect size. Multiple imputations will be used for missing data. The variables used in the imputation mode will be previous EPDS score, education level and parity. All patients’ demographic data, retrieved from web survey, will be analysed by descriptive (mean, median and range) statistics. For categorical variables, absolute frequency, percentages and/or proportions will be calculated. χ^2^ or Fisher’s exact test will be used for comparison between groups. For the primary outcome measure, a two-sided p value of <0.05 will be considered significant. Subgroup analyses will be performed for several subgroups of EPDS scores. Spearman’s correlation test will be used to test the correlation between maternal antenatal mental health characteristics assessed by EPDS, GAD7 and IES-R at <34–36 weeks and at 6 weeks postpartum.

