### Outcome measures

The primary outcome measure is the woman’s EPDS assessed at 34–36 weeks of gestation and at 4–6 weeks postnatally.

Secondary outcomes are GAD7 scores to assess maternal anxiety levels, IES-R score to assess PTSD and pregnancy complications, including occurrence of mental health disorders, rate of preterm birth, rate of induction of labour, rate of vaginal birth, elective caesarean sections on maternal request as well as other birth outcomes.

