#### Psychological assessments

EPDS^41 42^ is a widely validated screening instrument. A high EPDS score does not in itself confirm a diagnosis of depression. A score above a certain cut-off point may, however, indicate probable depressive disorder. In the present study, the EPDS will be administered in the third trimester of pregnancy (a 34–36 weeks) and at 4–6 weeks postpartum. An EPDS cut-off score of >10 has been found to be optimal for perinatal screening for depression.^43^

*The* GAD7 questionnaire^44 45^ has been translated into Chinese and validated in general hospital outpatients, with a cut-off score of >10^22^ to indicate anxiety.

IES-R will be used to assess PTSD. It has been translated and validated in Chinese^46–48^ to assess symptoms of PTSD corresponding with Diagnostic and Statistical Manual of Mental Disorders (DSM-V).^46 47^ A survey about COVID-19 will also be administered at the same time points (at 34–36 weeks of gestation and 4–6 weeks postpartum).

The EPDS, GAD7 and IES-R scales were chosen over psychodiagnositc interviews because they show high reliability and validity and are more cost-effective and efficient compared with psychodiagnostic interviews.^49^

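### The prenatal-versus-postnatal comparison of the same women is assigned an independent-sample t-test, which gives that within-woman comparison the wrong standard error; the between-arm contrasts are not affected.

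*Protocol article*

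**What the plan says.** Under Statistical methods, the protocol article states that mean EPDS, GAD7 and IES-R scores "will be compared between the intervention and control groups and across time points (prenatal and postnatal), using independent sample t-tests". One sentence names two comparisons, between arms and between visits, and assigns one test to both.

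The two visits involve the same participants. Under Outcome measures: "The primary outcome measure is the woman’s EPDS assessed at 34–36 weeks of gestation and at 4–6 weeks postnatally". Under Psychological assessments: "the EPDS will be administered in the third trimester of pregnancy (a 34–36 weeks) and at 4–6 weeks postpartum".

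The fallback for skewed scores is also a test for independent samples: "The non-normally distributed continuous variables will be analysed with the Mann-Whitney U test". The article names no paired t-test, signed-rank test or repeated-measures model. The same section also says that "Spearman’s correlation test will be used to test the correlation between maternal antenatal mental health characteristics" and goes on to mention the late-pregnancy and 6-week postpartum assessments. The authors therefore appear to expect the two measurements to be linked within a woman.

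**The concern.** An independent-sample t-test takes the variance of the difference between two means as the sum of their variances. When both means come from the same women, the covariance between visits must be subtracted. Leaving it out gives the wrong standard error, confidence interval and p value for change from late pregnancy to the postnatal visit.

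This is not a detail left to a separate analysis plan. The article names a specific test, and for this comparison it is the wrong one. At stake is the trial's description of how depression, anxiety and stress scores move across delivery: a real shift could be reported as no significant change.

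There is also a risk in interpretation. If change over time is tested separately in each arm, a significant result in one arm and not in the other may be read as an effect of the intervention. It is not one.

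**Working it through.** **Inputs from the protocol article (Sample size and power calculation; Statistical methods).** "EPDS scores show a normal distribution with a mean of 12.5 and SD of 4.0". The target is "to detect a 20% difference in mean EPDS scores between the intervention versus control groups", so 0.20 × 12.5 = 2.5 points, "with a 80% power and an alpha of 0.05 in each study location", two-sided, with 40 women per arm and 80 per city.

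**Assumptions, not in the document.** Within-woman correlation r of 0.3, 0.5 and 0.7; SD 4.0 at both visits; an illustrative change over time of 1.5 EPDS points.

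**Step 1: the plan's own figure.** n per arm = 2 × [4.0 × (1.960 + 0.842) / 2.5]² = 40.19. Rounded up this is 41, against 40 stated; power with 40 per arm is 79.8%. The stated size reproduces to within rounding. It is for a between-arm difference, for which an independent-sample test is correct.

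**Step 2: standard error of the prenatal-minus-postnatal mean difference in m women.**

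- Independent formula: SD × √(2/m). With m = 40: 4.0 × √(2/40) = 0.894.
- Paired formula: SD × √(2(1 − r)/m).
- Ratio: 1/√(1 − r), whatever the value of m.

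**Step 3: actual size of the nominal 5% independent test.** Approximately 2 × [1 − Φ(1.96/√(1 − r))]. At r = 0.5: 2 × [1 − Φ(2.77)] = 0.56%. Simulation with 20,000 runs agrees closely.

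| r | SE independent (m = 40) | SE paired (m = 40) | Overstatement | Actual size, formula | Actual size, simulated (m = 40) |
|---|---|---|---|---|---|
| 0.3 | 0.894 | 0.748 | 20% | 1.9% | 1.9% |
| 0.5 | 0.894 | 0.632 | 41% | 0.56% | 0.66% |
| 0.7 | 0.894 | 0.490 | 83% | 0.03% | 0.06% |

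The paired test holds its size, at about 5% in the same simulations. The independent test is correct only at r = 0. With a negative correlation the error reverses: at r = −0.2 the actual size is about 7.4%.

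**Step 4: power for the assumed 1.5-point change, m = 40, r = 0.5, normal approximation.**

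- Independent test: it rejects when the observed difference exceeds 1.96 × 0.894 = 1.753, while the true standard error is 0.632. Power = 1 − Φ((1.753 − 1.5)/0.632) = 1 − Φ(0.40) = 34.5%.
- Paired test: power = Φ(1.5/0.632 − 1.96) = Φ(0.41) = 66%.

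Simulated t-tests give slightly lower values and show the dependence on r and on the number of women:

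| r | m = 40, independent | m = 40, paired | m = 80, independent | m = 80, paired |
|---|---|---|---|---|
| 0.3 | 36% | 50% | 68% | 80% |
| 0.5 | 34% | 64% | 71% | 91% |
| 0.7 | 30% | 85% | 76% | 99% |

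Here 40 women is one arm in one city and 80 is both arms in one city.

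**The case against.** **The sentence may mean something else.** It can be read as saying that the arms are compared at each of the two visits, and independent t-tests would then be right. The Analysis plan subsection lends some support: it mentions only direct comparison of the two groups. The reading is possible, but the sentence does not say it. Visits are listed as something compared, alongside the arms. At the least the wording needs correction, and the fix below covers both readings.

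**A reader might infer that the efficacy p values are wrong.** The documents do not support that. The primary objective is the impact of the intervention on EPDS, and the sample size is for intervention versus control. At one visit the two arms contain different women, so the independent t-test is valid. Step 1 shows that the planned size rests on that contrast.

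**A reader might also infer that the plan fails for lack of a test of whether the intervention alters the course from pregnancy to postpartum.** No stated objective asks that question. Both assessments follow the two support sessions (18–22 and 24–28 weeks), so the prenatal-to-postnatal difference is not in itself a treatment effect. A direct test is needed only if such a claim is to be made.

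**The error is conservative and its size is assumed.** Both points stand. With positive correlation the wrong test produces too few significant results, not too many. Neither r nor the 1.5-point change comes from the document, and 40 women is the small-sample case. The loss of power shrinks with more women. With 160 (two cities of 80) and r = 0.5, the independent standard error is 4.0 × √(2/160) = 0.447 and the paired one 0.316; the normal approximation then gives about 98% against more than 99%. The overstatement of the standard error does not shrink: it depends on r alone.

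**Conclusion.** The point holds for the comparison over time and no further. As written, the plan applies a test for independent samples to two measurements of the same women on all three scales, and its non-parametric fallback has the same fault. Under the assumed range of r, the standard error is 20% to 83% too large, and the nominal 5% test runs at about 1.9% falling to about 0.05%. At r = 0.5 an assumed 1.5-point change would be detected with power of about 35% rather than 66% in 40 women, and about 71% rather than 91% in 80. The direction depends on r being positive, which is expected but not documented. Severity is moderate: a secondary comparison is wrong, while the treatment contrast at each visit and the 40 per arm remain sound.

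**What to change.** Split the sentence into two rules.

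- **Between arms, at each visit:** keep the independent-sample t-test, with Mann-Whitney U for non-normal scores.
- **Within women, prenatal to postnatal:** use a paired t-test, with the Wilcoxon signed-rank test for non-normal differences.

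If a difference between arms in change over time is to be claimed, test it directly, by comparing change scores between arms or through an arm-by-visit term in a mixed model. It should not be inferred from separate tests within each arm.

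If the intent was only to compare the arms at each visit, reword the sentence to say that; no new test is then needed.

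The cost is analysis wording only: no added participants, visits or data. It is best settled before outcome data are examined by arm.

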### Previous research

Screening programmes appear to be effective in identifying pregnant women at risk of developing perinatal mental health disorders,^25^ but they are neither universally implemented in public healthcare nor necessarily lead to effective interventions. One reason for the limited effectiveness is the small number of multidisciplinary perinatal mental healthcare teams that provide for the assessment and treatment of perinatal mental health disorders.^26^ Pregnant women in Shanghai reported a lack of access to resources and a strong preference for web-based psychosocial support. Previous studies suggested that women who received a peer support intervention were at half the risk of developing postnatal depression at 12 weeks postpartum than those in a control group.^27 28^ A recent systematic review has shown that therapist-supported internet-based cognitive behavaroral therapy (iCBT) significantly improves stress, anxiety and depressive symptoms among postpartum women, although the magnitude of effect was variable.^29^

There are challenges associated with supporting a family and raising children for young people living in modern metropolitan urban areas. These challenges may have a negative effect on maternal mental health. In Shanghai, China, a previous Randomized control trial (RCT) at the Obstetrics and Gynaecology Hospital of Fudan University concluded that a prenatal evidence-based psychosocial intervention model for high-risk pregnant women holds potential as a preventive programme that can address maternal health and improve birth outcomes.^30^ The mental health statuses of 6024 pregnant women were investigated when they registered for prenatal care from September 2015 to August 2016, where 23.89% and 9.44% had symptoms of depression and anxiety, respectively.^30 31^ There is a significant positive association between parity, depression, older age and risk of developing PPD.^32 33^ A cross-sectional study of 842 pregnant women with obstetric complications attending the same hospital reported that the prevalence of major and minor depression in high-risk pregnant women during antenatal period was 8.3% and 28.9%, respectively.^32^

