### Recruitment and blinding

Pregnant women will be recruited via non-profit organisation websites in each country. In addition to Hong Kong and Shanghai, we aim to include additional urban locations, including Stockholm, Sweden in this multicenter study. Via web link, the women will be guided to the research project website. The peer support website includes information about the project and informed consent. By completing the initial sociodemographic survey, the women can consent to participate in the research study. Then, they will ask to use an app to follow the study and complete the survey questionnaires. The participating women will be automatically randomised to intervention (peer-to-peer web-based psychosocial support) or control group (standard care) by the computer-generated random sequence. Regardless of recruitment to the intervention or control group, the women will continue their regular visits at the maternity clinics as usual.

Both the women and their peers will be forbidden to inform anyone in the study about which study group they belonged to. However, due to the nature of intervention, investigators, as well as the study participants, will not be blinded to the intervention.

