#### Analysis plan

The EPDS, GAD7 and IES-R scores between intervention and control groups will be directly compared. We will also compare the proportions of women with EPDS score of >10 and>15 in the two groups.

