#### Confounders

Socioeconomic status, educational level, parity, obstetric history including history of complications and trauma during previous pregnancies, number of surviving children, history of chronic diseases and use of medication, complications developing during current pregnancy (such as preeclampsia, gestational diabetes etc) may all be confounders.

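### The only between-arm method stated for mean EPDS is an unadjusted t-test; a linear model with parity and education would be a cheap, probably modest improvement

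*Protocol article*

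**What the plan says.** The Outcome measures section defines the primary outcome: "The primary outcome measure is the woman’s EPDS assessed at 34–36 weeks of gestation and at 4–6 weeks postnatally". Statistical methods says mean scores will be "compared between the intervention and control groups and across time points (prenatal and postnatal), using independent sample t-tests", and the Analysis plan section repeats the idea: "The EPDS, GAD7 and IES-R scores between intervention and control groups will be directly compared". The other between-arm tools named are Mann-Whitney for non-normal variables and χ² or Fisher tests for proportions. None of these adjusts for covariates.

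Two background factors have a role elsewhere. For missing data the article says: "The variables used in the imputation mode will be previous EPDS score, education level and parity". The Confounders section opens with "Socioeconomic status, educational level, parity, obstetric history including history of complications and trauma during previous pregnancies" and goes on to chronic disease, medication and complications arising in the current pregnancy. It says these may be confounders but attaches them to no analysis. Previous research adds: "There is a significant positive association between parity, depression, older age and risk of developing PPD".

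On timing, Recruitment and blinding says "By completing the initial sociodemographic survey, the women can consent to participate in the research study", after which women are "automatically randomised to intervention (peer-to-peer web-based psychosocial support) or control group (standard care) by the computer-generated random sequence". No stratification factor is stated.

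**The concern.** The article treats education and parity as informative enough about EPDS to impute it, and as possible confounders, but no stated comparison of the arms uses them. Two things are at stake.

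- **Precision.** EPDS variance explained by these factors stays in the error term of a t-test. The sample size is set for each city at 40 per arm, where planned power is about 80% with no margin.
- **Chance imbalance.** With 40 per arm and no stratification stated, the arms of one city can differ noticeably on parity or education, and the stated test does not correct for that.

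There is also a smaller drafting matter. The Confounders list mixes background factors with complications that can arise after randomisation and gives no rule for use. If adjustment is done later, nothing stated settles which variables are admissible.

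The point is confined to parity and education. It does not ask for a baseline EPDS, since the Psychological assessments section schedules EPDS only at 34–36 weeks and at 4–6 weeks postpartum.

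**Working it through.** **Inputs from the Sample size section:** mean EPDS 12.5, SD 4.0, difference 20%, power 80%, alpha 0.05, 40 per arm per city, 100 per city with dropout. The two-sided test is from Statistical methods.

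**Inputs assumed:** R², the share of EPDS variance explained by parity and education, with a range of 0 to 0.25 shown; one degree of freedom for each factor (k = 2); 50% prevalence for a binary factor in the imbalance check.

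**1. The plan's own figure.** The difference is 0.20 × 12.5 = 2.5 points, so d = 2.5/4.0 = 0.625. The normal-approximation size is n = 2(1.96 + 0.842)²/0.625² = 40.2, which rounds up to 41 per arm against 40 stated. That is agreement for practical purposes. At 40 per arm the noncentrality is 0.625 × √(40/2) = 2.795 on 78 df, and exact noncentral-t power is 78.8%. A dropout of 20%, implied but not stated, gives 80/0.80 = 100 per city.

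**2. Power with adjustment, one city.** Adjustment changes the standardised difference to 0.625/√(1 − R²). The degrees of freedom become 78 − 2 = 76. As a conservative charge for estimating the covariates, the noncentrality is multiplied by √(76/78).

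| Assumed R² | Power, 40 per arm | Change from 78.8% |
|---|---|---|
| 0 | 77.8% | −1.0 |
| 0.02 | 78.6% | −0.2 |
| 0.05 | 79.8% | +1.0 |
| 0.10 | 81.9% | +3.1 |
| 0.15 | 84.0% | +5.2 |

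Break-even is at R² of about 0.03.

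**3. Power if the two cities are pooled.** With 80 per arm, unadjusted power for the same difference is 97.6%. With three covariates (parity, education, city) it is 97.9% at R² = 0.05, 98.8% at 0.15 and 99.4% at 0.25. The gain is therefore at most about 2 points, because there is little left to gain.

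**4. Chance imbalance.** For a 50% binary factor, the SE of the between-arm difference in proportions at 40 per arm is √(2 × 0.25/40) = 0.112. The chance of a gap of 15 percentage points or more is about 18% (normal approximation). At 80 per arm it is about 6%.

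**5. What such an imbalance does to the estimate.** A 50% binary factor explaining a share R² of the variance implies an EPDS gap of √(R² × 16/0.25) between its two levels.

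- At R² = 0.05 the gap is 1.79 points, so a 15-point imbalance shifts the estimate by 0.15 × 1.79 = 0.27 points.
- At R² = 0.02 the gap is 1.13 points and the shift is 0.17 points.

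The SE of the treatment difference is 4.0 × √(2/40) = 0.89 and the target difference is 2.5. The shift is thus about 0.3 SE or less at these values.

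**The case against.** The strongest reply is that nothing is stated wrongly. In a randomised trial the t-test is unbiased over randomisation, keeps its type I error, and matches the comparison for which the trial was sized. Its standard error already reflects random covariate imbalance. All of this stands, and it limits the point to an improvement.

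A reader might infer several stronger things that the article does not support:

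- **That precision is certainly being lost.** No R² is given. The association cited under Previous research concerns risk of postpartum depression, gives no strength and does not mention education. At R² of about 0.03 or below there is no gain.
- **That each city is the unit of the primary analysis.** The sample size is set per city, but the primary objective covers Hong Kong and Shanghai together, and the abstract leaves city differences to subgroup analyses. The article does not settle this.
- **That no planned analysis would handle an imbalance.** This is a condensed article, and a supplementary adjusted model could be in a full analysis plan that is not shown. What can be said is that the stated primary method is unadjusted.
- **That the Confounders section contradicts the t-test.** It says only that the factors may be confounders and does not say of which analysis. It could serve the objective relating mental health to elective caesarean section. Using a variable for imputation creates no duty to adjust for it.
- **That maternal age is available as well.** The contents of the entry survey are not listed. Parity and education must be collected because the imputation needs them, but their recording before randomisation is inferred, and age is not shown to be recorded at all.

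What remains is that the article names the primary test, so this is a stated choice and not a detail left open, and the alternative needs no new data.

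**Conclusion.** The point holds as a low-severity suggestion. The stated comparison of mean EPDS leaves unused two factors that the article itself treats as informative, and a pre-specified linear model would use them at almost no cost. On the plan's inputs the effect at 40 per arm runs from a loss of about 1 power point, if the covariates explain nothing, to a gain of about 5 points at R² = 0.15. With pooled cities it is at most about 2 points. Protection against chance imbalance is real but small, at about 0.27 EPDS points for a 15-point imbalance in a factor explaining 5% of the variance. These sizes rest on assumed values of R² and prevalence and on one degree of freedom per factor; the article gives none of these. The validity of the t-test is not in question.

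**What to change.** **Statistical methods.** Make the primary analysis a linear model of EPDS at each primary visit, with terms for arm, parity and education level as recorded before randomisation, plus city if the cities are pooled. Fit it in each imputed dataset, combine the results, and report the adjusted mean difference with its 95% CI. Keep the independent-sample t-test as a sensitivity analysis. Fix the coding of parity and education in advance, with few categories, and confirm that the entry survey records both.

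**Confounders.** State that only factors recorded before randomisation enter this model, so that complications developing during the current pregnancy are excluded. Describing the retained factors as prognostic covariates would suit a randomised comparison better.

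**Cost.** Wording in two sections and a standard regression, with no added women or data. The downside is a few degrees of freedom, worth about 1 power point at 40 per arm if the covariates explain almost no variance. The change should be made before outcome data are seen by arm.

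### The listed multiple-imputation variables omit randomised arm; followed as written, this biases the primary EPDS difference toward zero, mostly at 34–36 weeks

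*Protocol article*

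**What the plan says.** The Statistical methods section commits to imputation ("Multiple imputations will be used for missing data") and then names the predictors: "The variables used in the imputation mode will be previous EPDS score, education level and parity". The sentence is a definite list, with no wording to mark it as a set of examples. Nothing in the article says that imputation is done within arm.

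The same section compares mean scores between intervention and control "using independent sample t-tests", with no covariate adjustment described. Outcome measures sets two primary time points: "The primary outcome measure is the woman’s EPDS assessed at 34–36 weeks of gestation and at 4–6 weeks postnatally". Psychological assessments gives the same two occasions and no earlier one: "the EPDS will be administered in the third trimester of pregnancy (a 34–36 weeks) and at 4–6 weeks postpartum".

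**The concern.** An imputation model should contain every variable in the analysis that follows it. Here the analysis has one explanatory variable, the randomised arm, and the listed model lacks it. Missing scores in both arms are then drawn from a single distribution that averages over the arms. Mixing those draws with the observed scores dilutes the arm difference.

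The dilution has a known direction and grows with the missing share. Recruiting more women under the same model would not remove it. At stake is a real benefit being under-reported, or missed, at one or both primary time points.

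**Working it through.** **Inputs from the protocol article.** Sample size and power calculation gives the target, "to detect a 20% difference in mean EPDS scores between the intervention versus control groups", and the distribution: "EPDS scores show a normal distribution with a mean of 12.5 and SD of 4.0". So the difference is δ = 0.20 × 12.5 = 2.5 and σ = 4.0. That section also gives 80% power, alpha 0.05, 40 per arm and 80 per city, raised to 100 per city. The implied dropout is 1 − 80/100 = 20%; no rate is stated. The two-sided test is in Statistical methods.

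**The plan's own figure.** n per arm = 2 × [σ(1.960 + 0.842)/δ]² = 2 × (4 × 2.802/2.5)² ≈ 40.2. The stated 40 is reproduced, and 40 per arm gives 79.8% power.

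**34–36 week EPDS, or women missing both scores.** Let m be the missing share, equal in both arms. Education and parity are balanced by randomisation, so imputed values have an expected arm difference of 0:

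E(estimate) = (1 − m)δ + m × 0 = δ(1 − m)

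- m = 0.10: 2.5 × 0.90 = 2.25
- m = 0.20: 2.5 × 0.80 = 2.00
- m = 0.30: 2.5 × 0.70 = 1.75

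With unequal missingness the factor is the harmonic mean of the two retention proportions. For 10% and 30% missing it is 2 × 0.9 × 0.7/(0.9 + 0.7) = 0.79, so the bias is still toward zero.

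**Postnatal EPDS with the 34–36 week score observed.** Assume the same δ at both visits and a within-arm correlation r. Ignoring arm, and leaving aside education and parity, the slope of the later score on the earlier one is

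b = (rσ² + δ²/4)/(σ² + δ²/4) = (16r + 1.5625)/17.5625

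The imputed difference is bδ, and E(estimate) = δ[(1 − m) + mb]. At m = 0.20:

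- r = 0.3: b = 0.36, imputed difference 0.9, estimate 2.18
- r = 0.5: b = 0.54, imputed difference 1.4, estimate 2.27
- r = 0.7: b = 0.73, imputed difference 1.8, estimate 2.36

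**Simulation.** Settings: 50 per arm, equal missingness completely at random, normal linear imputation with parameter draws, 20 imputations, Rubin's rules with small-sample degrees of freedom, and 1,500 trials per setting. Education was given a correlation of 0.2 with EPDS; parity was unrelated to it.

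| Setting | Arm omitted: estimate, power | Arm included: estimate, power |
|---|---|---|
| 34–36 weeks, 10% missing | 2.27, 77% | 2.53, 84% |
| 34–36 weeks, 20% missing | 1.97, 61% | 2.52, 77% |
| 34–36 weeks, 30% missing | 1.77, 43% | 2.53, 73% |
| Postnatal, 20% missing, r = 0.3 | 2.22, 72% | 2.50, 79% |
| Postnatal, 20% missing, r = 0.5 | 2.26, 76% | 2.49, 80% |
| Postnatal, 20% missing, r = 0.7 | 2.37, 82% | 2.51, 84% |

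A separate simulation at 34–36 weeks and 20% missing gave 1.98 and 60% without arm, and 2.48 and 77% with it. At 30% missing, power across simulations was 39–43% without arm and 71–73% with it. Under no true effect at 34–36 weeks with 20% missing, rejection was 1.3–1.6% without arm and 4.5–4.7% with it.

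**A benchmark.** At 20% missing, simply dropping the missing women leaves 50 × 0.80 = 40 per arm. Under the same assumption that analysis is unbiased, with 79.8% power. The imputation as listed does worse than no imputation.

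**The case against.** **The list may not be exhaustive.** The article does not say that only these variables will be used, and imputing separately by arm would fit the sentence, because arm would then be a stratifier. An unseen analysis plan may say so. A reader might infer that the final analysis will certainly leave arm out; the article does not establish that. What stands is that the published rule omits arm, and anyone who follows it gets the bias.

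**An earlier EPDS may exist.** Figure 1 is not shown, and the reference to a previous EPDS score may point to one. The article's text gives no such assessment, but its absence cannot be proved. It would alter the power figures. It would not remove the bias, because a pre-randomisation score is balanced between arms and cannot carry a treatment effect.

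**Not every imputed value loses the effect.** A reader might infer that imputed scores carry no treatment effect anywhere. The plan does not support that: a postnatal score imputed from an observed 34–36 week score keeps about 36–73% of it at correlations of 0.3–0.7. This objection stands in full.

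**The size rests on assumptions.** The 20% share is inferred, and at 10% the loss is modest. The calculations also give women with missing scores the full 2.5-point benefit. If those lost before the support sessions had less, the true difference would be smaller and so would the bias. That stands as a limit on size. A conservative assumption of that kind belongs in a declared sensitivity analysis and should not arise by omission.

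**The error is conservative.** This is correct. A reader might fear more false positives; the simulations show fewer.

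**The analysis-set wording is a separate matter.** The phrase "Data will be analysed per protocol using an intention-to treat method" may mean only that the analysis is done as the protocol specifies. Nothing here depends on it.

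**Conclusion.** The point holds for the rule as published: the predictors named for imputation omit the variable that the primary analysis tests, and the resulting bias is toward zero.

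At 34–36 weeks the estimate is attenuated in proportion to the missing share. The cost is about 0.5 of 2.5 points and some 16–17 percentage points of power at 20% missing, with less at 10% and more at 30%. For the postnatal score at 20% missing, the estimate falls to about 2.2–2.4 and power by up to about 7 percentage points. Women missing both scores follow the 34–36 week pattern.

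These sizes assume a true difference of 2.5 at both visits, SD 4, 50 per arm, values missing completely at random, and correlations of 0.3–0.7. The direction needs less: a real effect, and missingness unrelated to the scores within each arm. Confidence is high about the published list and the direction, and moderate about the size.

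**What to change.** Amend the imputation sentence to state that randomised arm and study city are in the model together with the variables already listed, or that imputation is done separately by arm. City is added because the sample size is set per city; no separate bias from its omission has been quantified. State also which assessment the previous EPDS score refers to, for each of the two primary time points.

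The cost is one or two sentences, settled before any data are examined by arm. Arm and city are already recorded, no new data are needed, and including them has no material downside.
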